## Methods

### Study design and setting

The VA is divided into different regional systems of care across the U.S. called Veterans Integrated Service Networks (VISNs). This multicenter interventional study focused on the Midwest VISN, which includes 8 VA health systems across Minnesota, Iowa, North Dakota, South Dakota, and Nebraska. Eligible Veterans are assigned to either a targeted pharmacy intervention or usual care. The study began in February 2022 and will continue until all eligible Veterans in the region are offered the intervention, which is anticipated to be in 2025.

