### Outcomes

Our primary outcome is initiation of an SGLT2i among patients deemed candidates for SGLT2i as determined by the VA dashboard. Patients who filled an SGLT2i at any point during the study timeframe, as determined by electronic health record data, will be considered to have initiated the medication.

Secondary outcomes will include adherence to the medication 12 months after initial prescribing (defined by refills of their SGLT2i), as well as various process and safety measures, such as the number and percent of patients who obtained metabolic labs after SGLT2i initiation, abnormal lab results, including acute kidney injury, and defined reasons for declining or stopping the medication (including low blood pressure/hypotension and hypoglycemia). Secondary outcomes will also include the proportion of patients who decline the intervention and later obtain an SGLT2i from another source (which will be reported as a descriptive statistic only as Veterans in the usual care, unlike those in the intervention arm, cannot crossover to the alternative arm). In addition, we will examine the progression of kidney disease, defined as a 40% reduction in eGFR sustained for at least two measures. We will also measure the number of times eGFR is assessed as this may affect outcome ascertainment.

Exploratory outcomes will include rates of all-cause hospitalizations, initiation of dialysis, and major adverse cardiac events (nonfatal myocardial infarction, nonfatal stroke, and hospitalization for heart failure).

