### Analysis

We will assess balance in baseline clinical and demographic characteristics between the two study arms with chi-square tests for categorical variables (e.g., patient sex) and Kruskal-Wallis test assuming unequal variances for continuous variables (e.g., patient age, baseline eGFR as calculated by the final serum creatinine concentration before the index date via the most recent CKD-EPI equation) [28]. The primary and secondary outcomes, the proportion of initiation of SGLT2i or proportion with a safety or process measure, respectively, will be compared between the study arms via the Two-Sample Proportions test. For binary exploratory outcomes, such as initiation of dialysis, major adverse cardiac events, and progression of kidney disease, we will also compare proportions between the arms via Two-Sample Proportions test. When these binary outcomes have an associated time of occurrence, Kaplan-Meier analysis will be used to assess the cumulative incidence of these events. We will use logistic regression and Cox proportional hazards models for adjusted analyses accounting for patient medical and demographic characteristics for binary and time-till-event outcomes. A Type-I-Error rate of 0.05 will be used for the primary outcome to declare significance and we will report the associated 95% confidence interval. Secondary outcomes will also use a p-value of < 0.05 and 95% confidence intervals.

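### Kaplan-Meier is named as the cumulative-incidence estimator for outcomes that death precludes, and a first event that is a fatal infarct or stroke enters neither MACE nor any death outcome (minor)

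*Protocol article*

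**What the plan says.** The Analysis section of the protocol article names the outcomes: "For binary exploratory outcomes, such as initiation of dialysis, major adverse cardiac events, and progression of kidney disease". It compares these as proportions between arms. Where the outcome has a time of occurrence, it adds that "Kaplan-Meier analysis will be used to assess the cumulative incidence of these events". For adjustment it says "We will use logistic regression and Cox proportional hazards models for adjusted analyses".

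The Outcomes section defines the composite as "major adverse cardiac events (nonfatal myocardial infarction, nonfatal stroke, and hospitalization for heart failure", with no fatal component. The exploratory list reads "Exploratory outcomes will include rates of all-cause hospitalizations, initiation of dialysis, and major adverse cardiac events". Kidney progression is "defined as a 40% reduction in eGFR sustained for at least two measures". Death, from any cause or cardiovascular, is not a primary, secondary or exploratory outcome. The article gives no rule for handling deaths in the time-to-event analyses. The Background names lower cardiovascular mortality as one of the benefits of the drug class.

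**The concern.** The population has type 2 diabetes and an eGFR from 25 to below 60. A patient who dies cannot later start dialysis, have a nonfatal infarct or stroke, or provide the second eGFR that confirms progression. Kaplan-Meier with deaths censored treats the dead as if they could still have the event at the same rate as survivors. Its complement then estimates incidence in a world without death, and is higher than the share of patients who actually have the event. The direction of the error is known.

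The definition of MACE is a second, separate matter. A patient with no earlier component who dies of an infarct or stroke meets no MACE component and appears in no death outcome. At stake are the reported incidences of these outcomes and the reader's ability to see whether the arms differ in deaths.

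**Working it through.** **No figure to reproduce.** The article states no event rate, death rate, event count or sample size. Every rate below is an assumption chosen to show a range.

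**Horizon.** The Study design and setting section says "The study began in February 2022 and will continue until all eligible Veterans in the region are offered the intervention", and anticipates this in 2025. I take 3 years as roughly the longest follow-up and 1 year as a short one.

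**Formulas.** With constant hazards h (event) and d (death), and horizon t:
- one minus Kaplan-Meier, deaths censored: 1 − exp(−h·t)
- cumulative incidence with death competing (the Aalen-Johansen target): h/(h+d) × [1 − exp(−(h+d)·t)]

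Example with h = 0.08, d = 0.08, t = 3: 1 − exp(−0.24) = 21.3%, against 0.5 × [1 − exp(−0.48)] = 19.1%. The ratio is 1.119, a 12% relative overstatement.

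| t (years) | h per year | d per year | 1 − KM | Cumulative incidence | Relative excess |
|---|---|---|---|---|---|
| 3 | 0.08 | 0.05 | 21.3% | 19.9% | 7.4% |
| 3 | 0.08 | 0.08 | 21.3% | 19.1% | 11.9% |
| 3 | 0.08 | 0.12 | 21.3% | 18.0% | 18.2% |
| 3 | 0.01 | 0.05 | 2.96% | 2.75% | 7.6% |
| 3 | 0.01 | 0.08 | 2.96% | 2.63% | 12.4% |
| 3 | 0.01 | 0.12 | 2.96% | 2.48% | 19.0% |
| 1 | 0.08 | 0.05 | 7.69% | 7.50% | 2.5% |
| 1 | 0.08 | 0.12 | 7.69% | 7.25% | 6.0% |
| 1 | 0.01 | 0.05 | 1.00% | 0.97% | 2.5% |
| 1 | 0.01 | 0.12 | 1.00% | 0.94% | 6.1% |

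The relative excess depends mainly on the death hazard and the horizon, and hardly on the event hazard. In absolute terms it runs from about 0.02 percentage points (h = 0.01, d = 0.05, 1 year) to 3.3 points (h = 0.08, d = 0.12, 3 years).

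**The proportions test.** Suppose all patients are followed to a common horizon. The crude proportion with the event then counts a patient who dies first as never having had it, exactly as the cumulative incidence function does. With h = d = 0.08 over 3 years, a simulation of 2 million patients gave a crude proportion of 19.1%, equal to the formula.

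**The fatal component.** Let nonfatal events have hazard a and fatal cardiac events hazard b, with no other deaths, at 3 years. The nonfatal-only incidence is a/(a+b) × [1 − exp(−3(a+b))]. With fatal events included it is 1 − exp(−3(a+b)).

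| a per year | b per year | Nonfatal only | With fatal events |
|---|---|---|---|
| 0.03 | 0.01 | 8.5% | 11.3% |
| 0.05 | 0.02 | 13.5% | 18.9% |
| 0.06 | 0.03 | 15.8% | 23.7% |

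Under these assumptions, the events left out of the composite amount to more than the estimator's bias.

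**The case against.** Several points on the other side stand.

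- **Proportions test.** A reader might infer that this test errs in the opposite direction, by scoring the dead as event-free, and should be dropped. The check above shows otherwise: with complete follow-up to a common horizon it targets the same quantity as Aalen-Johansen.
- **Between-arm comparison.** A reader might infer that Aalen-Johansen removes the effect of more survivors staying at risk in the arm with fewer deaths. It does not, because that effect is a property of cumulative incidence. With an equal event hazard of 0.05 and death hazards of 0.08 (control) and 0.06 (intervention), 3-year cumulative incidence is 12.4% against 12.8%, while one minus Kaplan-Meier is 13.9% in both arms. Cause-specific hazards answer that question, and the planned Cox models with deaths censored estimate them validly.
- **Likely size between arms.** The intervention is outreach, patients may decline, controls may receive the drug, and all dashboard patients are analysed. If uptake differs by 20 to 50 points and the drug lowers mortality by 15% (both assumed), the intervention arm's incidence becomes 12.46% to 12.53% against 12.42%, a difference of about 0.04 to 0.11 points.
- **Follow-up.** Sites join on a rolling basis and lists are drawn at several dates, so many patients have less than 3 years. At 1.5 years the relative overstatement is about 4% to 9%.
- **Handling of deaths.** The article does not say that deaths are censored. That is the usual Kaplan-Meier convention, but it is inferred here, and the full plan may say more.
- **Composite.** Counting only nonfatal events is a definitional choice. A patient with an earlier component is still counted, and a fatal event in hospital may appear under all-cause hospitalization. Replacing the composite with MACE or death would be a different endpoint, diluted by non-cardiac death.

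The objection does not remove the named pairing of Kaplan-Meier with cumulative incidence, or the absence of any death outcome.

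**Conclusion.** The point holds and is minor. As written, the plan would report cumulative incidences of dialysis, MACE and kidney progression that are too high: by about 2.5% to 6% in relative terms at 1 year and 7% to 19% at 3 years. This rests on constant event hazards of 1% to 8% per year, death hazards of 5% to 12% per year, and censoring at death. None of these figures comes from the article. Independently of those rates, a patient whose first event is a fatal infarct or stroke is in neither MACE nor any death outcome.

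A reader might infer that the trial's main result is at risk. The documents do not support that: the primary outcome is drug initiation, and its comparison does not rest on this estimator. Dialysis and MACE are exploratory. Kidney progression is at most secondary: the Outcomes section lists it with the secondary outcomes and the Analysis section calls it exploratory.

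**What to change.** 1. Replace one minus Kaplan-Meier with the Aalen-Johansen cumulative incidence, with death as a competing event, for dialysis, MACE and kidney progression.
2. Keep the Cox models, censor at death, and label the results as cause-specific hazard ratios.
3. Report all-cause death by arm, from the VA record, as an exploratory outcome.
4. Keep the nonfatal MACE as defined, and add MACE or death beside it as a prespecified sensitivity composite.
5. Keep the two-sample proportions test, and state the common horizon to which follow-up is complete.

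The cost is revised wording, standard software and a pull of vital status, with no new patients or visits. The downsides are slightly lower reported incidences and a sensitivity composite that includes non-cardiac deaths.

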### Aims

Improve the proportion of eligible Veterans with CKD initiated on an SGLT2i through a targeted pharmacy intervention across a series of Veterans Affairs (VA) clinics. In addition, this project aims to inform learning health systems by testing a pragmatic strategy to reach eligible patients.

We hypothesize that patients who receive a targeted pharmacy intervention during the first iteration will have a higher proportion of SGLT2i initiation than those receiving usual care while they await a future wave of this same interventional program.

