### Patient selection and randomization

As part of their Academic Detailing Diabetes Campaign and to monitor SGLT2i initiation, the VA developed a diabetes dashboard to identify patients who would benefit from an SGLT2i. The dashboard includes the above inclusion criteria and several other demographic and clinical variables. The dashboard is updated daily to reflect eligible patients. One included variable in the dashboard is patients’ social security number. Due to the finite availability of resources, we have utilized a pseudo-randomization of eligible Veterans to determine which Veterans within the VISN receive the intervention first, providing a natural comparison group in those Veterans who will be intervened upon later. For this study, patients with an odd social security number are put in the intervention arm, while those with an even social security number serve as the control. Patient lists will be extracted from the VA dashboard at fixed time points throughout the study and will be considered the dates of randomization. The controls will receive usual care until all eligible Veterans in the odd-numbered group have received the intervention. At that time, even-numbered Veterans will also begin to receive the intervention.

The intervention will be implemented in a rolling fashion, beginning with patients at the Minneapolis VA health system, and other clinics will be subsequently added as outreach is being completed.

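### The initiation comparison makes no use of baseline data already held, and the planned adjusted model is not put on the same scale; standardizing it to a difference in proportions would be a nearly free improvement

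*Protocol article*

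**What the plan says.** All references are to the protocol article.

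- **Hypothesis (Aims).** The intervention arm "will have a higher proportion of SGLT2i initiation than those receiving usual care".
- **Outcome (Outcomes).** It is binary: "Patients who filled an SGLT2i at any point during the study timeframe, as determined by electronic health record data, will be considered to have initiated".
- **Primary comparison (Analysis).** The proportions "will be compared between the study arms via the Two-Sample Proportions test". The section adds: "A Type-I-Error rate of 0.05 will be used for the primary outcome to declare significance and we will report the associated 95% confidence interval".
- **Adjusted analysis (Analysis).** "We will use logistic regression and Cox proportional hazards models for adjusted analyses accounting for patient medical and demographic characteristics". The logistic model serves the binary outcomes and the Cox model the time-to-event ones. The text names no effect measure for the logistic model and does not say how its result relates to the primary comparison.
- **Baseline data.** The Analysis section says: "We will assess balance in baseline clinical and demographic characteristics between the two study arms", with sex, age and baseline eGFR as examples. Under Patient selection and randomization: "The dashboard includes the above inclusion criteria and several other demographic and clinical variables".
- **Allocation (Patient selection and randomization).** "patients with an odd social security number are put in the intervention arm, while those with an even social security number serve as the control".

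**The concern.** The article plans two analyses of the same binary outcome and does not connect them. One is on the scale of the hypothesis but ignores the covariates. The other uses the covariates but, unless something more is done, is summarized on a different scale.

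Two things are at stake. The first is interpretation. Allocation follows the parity of the social security number, so if the balance checks show a difference between arms, readers will turn to the adjusted result. An odds ratio is not collapsible: it moves away from 1 when prognostic covariates enter the model, even if the arms are perfectly balanced. A gap between the crude and adjusted odds ratios could therefore be this property, correction of an imbalance, or both, and the reader could not tell which.

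The second is precision. Covariates that predict initiation can narrow the interval for the difference in proportions, and the primary analysis as written forgoes that gain.

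**Working it through.** The article gives no initiation rate, effect size, sample size or covariate strength, so it has no figure to reproduce. What follows is an illustration under stated assumptions.

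**Inputs**
- From the article: a binary outcome, an unadjusted comparison of two proportions, and allocation by odd or even number.
- Assumed: a 1:1 ratio; marginal initiation rates p0 (control) and p1 (intervention); and a single prognostic score X, standard normal and perfectly balanced, with effect s per SD on the logit scale (s = 0.5, 1.0, 1.5). Within an arm, these s values correspond to c-statistics of about 0.64, 0.75 and 0.82 to 0.83 at 10% v 30%.

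**Step 1: size of the odds ratio.** Solve for a and b in

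p0 = E[expit(a + sX)], p1 = E[expit(a + b + sX)]

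by Gauss-Hermite quadrature. The conditional odds ratio is exp(b). The marginal odds ratio is [p1/(1−p1)] / [p0/(1−p0)].

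For 10% v 30%: difference 0.30 − 0.10 = 0.20; risk ratio 3.0; marginal odds ratio (0.30/0.70)/(0.10/0.90) = 3.86.

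**Step 2: precision of the difference.** With n per arm:

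- unadjusted: n·Var = p0(1−p0) + p1(1−p1)
- adjusted (efficiency bound): n·Var = E[q1(1−q1)] + E[q0(1−q0)] + Var(q1−q0)/2, where q0 and q1 are the probabilities given X.

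For 10% v 30% at s = 1.0:
- unadjusted: 0.09 + 0.21 = 0.30
- adjusted: 0.1770 + 0.0817 + 0.0097/2 = 0.2635
- variance ratio 0.878; ratio of interval widths √0.878 = 0.937.

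| Assumed rates | Difference | Marginal OR | Conditional OR at s = 0.5 / 1.0 / 1.5 | CI width ratio at s = 0.5 / 1.0 / 1.5 |
|---|---|---|---|---|
| 5% v 15% | 0.10 | 3.35 | 3.44 / 3.76 / 4.37 | 0.989 / 0.956 / 0.910 |
| 5% v 20% | 0.15 | 4.75 | 4.94 / 5.60 / 6.88 | 0.987 / 0.952 / 0.906 |
| 10% v 20% | 0.10 | 2.25 | 2.31 / 2.50 / 2.82 | 0.985 / 0.942 / 0.887 |
| 10% v 30% | 0.20 | 3.86 | 4.06 / 4.69 / 5.84 | 0.982 / 0.937 / 0.883 |
| 20% v 40% | 0.20 | 2.67 | 2.80 / 3.19 / 3.83 | 0.977 / 0.922 / 0.861 |

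Within each row, the difference in proportions is the same at every covariate strength; only the conditional odds ratio moves.

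**Step 3: simulation.** Runs used 200 patients per arm on average, with 600 repetitions.

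- 10% v 20%, s = 1.0: unadjusted difference 0.100 (empirical SE 0.035); difference standardized from the logistic model 0.100 (SE 0.033); conditional odds ratio 2.55. Rejection rate 81% unadjusted, 85% for the logistic coefficient.
- No effect (10% v 10%, s = 1.5): conditional odds ratio 1.01. Rejection rate 5.3% unadjusted, 4.7% logistic.

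The standardized and unadjusted differences estimate the same quantity, and the standardized one is more precise. Under no effect, both tests hold their level within simulation error.

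**The case against.** The strongest reply is that nothing in the article is wrong here. The unadjusted test with its interval matches a hypothesis about proportions, and a supporting logistic model is conventional. The article never says that an odds ratio will be reported. A logistic model can be standardized, and that step and the covariate list may sit in an analysis plan that is not shown. All the rates and covariate strengths above are assumed. The larger shifts need covariates with a c-statistic of 0.75 or more, and nothing in the article shows that age, sex and eGFR predict initiation so well. With weak covariates the interval narrows by only 1% to 2%.

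All of this stands, and it limits the point to an improvement. It also rules out three stronger readings that a reader might infer:

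- **That the plan commits to a conditional odds ratio.** It names the model, not the summary; the odds ratio is only the default output.
- **That the adjusted effect will be larger than the primary one.** A ratio cannot be compared with a difference. The valid comparison is with the marginal odds ratio, and the conditional one is further from 1 only if covariates are prognostic and the effect is not null.
- **That the adjusted analysis is no check at all.** It shares the null with the primary test, so it checks direction and significance, and the planned balance comparisons check the allocation directly. If the arms are imbalanced, adjustment also removes that imbalance. What the logistic coefficient does not check directly is the size of the difference.

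The reply does not remove the choice that the article does state: an unadjusted primary comparison although baseline data are at hand, and an adjusted model that is not tied to the scale of the hypothesis.

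**Conclusion.** The point holds as a nearly free improvement of low severity. The primary test is valid, and no conclusion would be wrong because of it. The plan leaves some precision unused and, as written, sets no adjusted estimate on the scale of its hypothesis.

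At assumed rates of 5% v 20% and 10% v 30%, the interval for the difference would narrow by about 1% to 2% at s = 0.5, 5% to 6% at s = 1.0 and 9% to 12% at s = 1.5. Over all five rate pairs in the table, the ranges are about 1% to 2%, 4% to 8% and 9% to 14%. These results assume 1:1 allocation, a correctly modelled prognostic score and an estimator that reaches the efficiency bound. The scale argument does not depend on any particular rate, only on prognostic covariates and a non-null effect.

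**What to change.** Keep the logistic model and standardize it (g-computation). Fit it to all patients on the dashboard lists, predict each Veteran's probability of initiation under both arms, average over the whole set, and take the difference, with a robust or bootstrap 95% confidence interval. Name the covariates in advance: baseline eGFR, age, sex, VA health system and list date. Use the result as the primary estimate, or present it beside the unadjusted difference. The odds ratio can be supplementary.

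Suggested wording: *The adjusted analysis of SGLT2i initiation will be a logistic model with baseline eGFR, age, sex, VA health system and list date, standardized over all included patients to a difference in proportions with a 95% confidence interval.*

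The cost is one sentence and a few lines of code on a model already planned, with no new data. If the standardized estimate becomes primary, that choice should be recorded before outcomes are compared between arms. If an analysis plan already specifies this step, it need only be cross-referenced.

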## Discussion

Given the emergent evidence on the benefits of SGLT2i on cardiac and kidney health, initiating eligible patients on this medication is of great importance and aligns with current practice guidelines. However, changing clinician prescribing behavior is a challenge; [29, 30] therefore, relying on passive diffusion by waiting for clinicians to change their prescribing patterns may take significant time. To expedite the implementation of SGLT2i prescribing, implementation strategies that promote adoption and penetration are needed. Due to the favorable risk profile of SGLT2i [5, 7] and the availability of local laboratory testing as routine post-SGLT2i assessment, this medication class yields itself well to both pharmacist-led care and a time-limited intervention before returning to primary care.

This project tests the effectiveness of a pharmacist-driven medication outreach initiative as a strategy to accelerate the initiation of SGLT2i in a rolling fashion to eligible patients within the VA. It will also provide data on the frequency with which patients reject SGLT2i, either when offered or due to early side effects or concerns after initiation outside the confines of a randomized clinical trial. If deemed successful, such a project would also offer scalability in both the VA and other health systems utilizing clinical pharmacy services. In addition, the results of this work will not only illustrate the effectiveness of this strategy in initiating SGLT2i but may also have implications for increasing dissemination for other areas of guideline-concordant care.

Finally, this design method lends itself well to the principles of learning health systems. Having systems in place to rapidly generate evidence and support practice change are key to the continuous learning and improvement that occurs within a learning health system. The rolling nature of this initiative and our election to use social security number, which is effectively a randomly assigned number (in the final digit) at birth, to create an intervention arm has created a pseudo-randomized interventional trial. Similar pragmatic approaches should be explored with future quality improvement projects to facilitate study designs that are easily implementable yet have added rigor to produce generalizable findings.

